### Eligibility and recruitment

Participants in this study are patients with COPD admitted to the Department of Respiratory Medicine, Affiliated Hospital of Jilin University. The inclusion and exclusion criteria are shown below.

Inclusion criteria:
① Hospitalized patients diagnosed with COPD according to the Global Initiative for Chronic Obstructive Lung Disease criteria② Patients with clear consciousness, stable vital signs, and the ability to cooperate③ Patients who have given informed consent④ Adult patients⑤ Patients with a sputum viscosity classified by the same person as grade II or grade III which is characterized by the loss of humidifying function in the upper respiratory tract, as well as the loss of the mucociliary transport function, and impaired expectoration [28]

Exclusion criteria:
① Presence of neuromuscular disease or terminal disease② Presence of asthma or other respiratory diseases③ History of thoracic and abdominal trauma and surgery④ Presence of skin infection at the site of contact⑤ Presence of a cardiac pacemaker, artificial stent, artificial valve, or heart failure⑥ Presence of acute exacerbation of COPD or on a rehabilitation program

Patients meeting inclusion and exclusion criteria will be invited to participate in our research. Informed consent will be obtained from each participant. The recruitment process will be handled by an independent caregiver who is not involved in other procedures at the Medical Center in Changchun, China.

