### Outcome measurements

Outcome measures will be collected and analyzed by researchers blinded to the patients’ group allocation. All assessments will be performed at the commencement of the study and after the 1-week intervention, with the exception of assessments for sputum production and certain additional secondary outcomes (Fig. 1). Sputum production will be assessed after the 1-h intervention session and every 24 h during the week-long intervention period. Additional secondary outcomes will be collected only at the conclusion of the intervention. A summary of the outcome measures for the study is outlined in Table 1.

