#### Primary outcomes

The first primary outcome will be sputum viscosity calculated using a viscometer [29, 30]. After the collection of sputum from patients, in line with the instructions, the assistant will insert the sputum into the rotor in the viscometer and read the digital output. The sputum viscosity is calculated by the formula (sputum viscosity = viscometer reading × 10). Patients will be given calibrated containers [31] at the baseline visit and instructed to collect 24 h worth of sputum in the container, between 07:00 each morning and 07:00 the following morning. The outcome assessor will observe and record the volumes of sputum at the 1- and 24-h time points daily during the intervention period.

We hope to reduce obstruction by clearing the sputum in the respiratory tract. Therefore, we will use the same pulmonary function meter to perform a complete spirometry assessment before and after the intervention [32]. Vital capacity can reflect the obstruction of pulmonary function and airway obstruction will be determined by FEV_1_%. The relation between expiration in the first second of forced expiration (FEV_1_) and the full forced vital capacity (FVC) will be represented by FEV_1_%, with normal values being approximately 75%. Generally speaking, the FEV_1_% of COPD patients is less than 70%. We are investigating whether this can be improved. The outcome assessor will only record vital capacity and FEV_1_% from the spirometry. We will follow the recommendations of the American Thoracic Society and European Respiratory Society [33] in the lung function test. Patients will be assessed between three and eight times, and the three best measurements with variability of less than 5% or 200 ml will be recorded [34]. The oxygen saturation of COPD patients will be expressed as SpO_2_. Similarly, SpO_2_ will be determined by pulse oximetry from the right middle finger [35–37] before and after the intervention. Since SpO_2_ is also a variable parameter, the patient will receive three evaluations and the average of the results recorded.

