### Sample size

Since the trial was designed with three arms, analysis of variance was chosen to calculate the sample size. We will have 90% power at the significance level (alpha) of 0.15 with an effect size of 0.4 to detect significant differences in sputum viscosity. Based on previous studies [45, 46], we assume that the dropout rate of our trial will be about 20% after the week-long intervention. Thus, the total sample size was 75, with 25 patients in each of the three groups. The sample size was calculated using the software PASS 2019.

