### Data collection, management, and analysis

All patients’ data will be recorded by trained clinical researchers using a standardized case report form (CRF) and saved using the EpiData electronic database. To ensure the reliability of our study, the management of this trial will be conducted by the Trial Steering Committee (TSC). Main investigators and statisticians consist of our Trial Steering Committee, who will oversee the entire trial. Meetings will be held once a month to monitor the progress of the research and to share opinions when there are problems. The measurement data will be expressed by mean ± SD, and the count data will be expressed by frequency and percentage. A Kolmogorov-Smirnov test will be performed to analyze sample normality. Within-group changes in sputum viscosity, FEV_1_%, vital capacity, arterial oxygen saturation, quality of life, and the level of anxiety will be compared using a paired *t*-test or Wilcoxon test depending on the data distribution. Inter-group differences between baseline and post-intervention among the outcomes will be compared by one-way analysis of variance. According to the normality of the data distribution, a general linear model or multi-generalized linear model will be used to compare the differences between the primary and secondary outcomes after adjusting the covariates, including sociodemographic variables, such as sex, age, body mass index, smoking history, severity of disease, among others, and baseline variables. In addition, we will follow the principle of intention to treat (ITT) and use the sequence mean method to deal with the missing data to analyze the results of the comparison between groups of each outcome. To assess whether the missing data will affect the results of the study, we will compare participants who did not complete the intervention with those who completed the intervention to verify the sensitivity of the results of the trial. A two-tailed *p*-value of < 0.05 will be taken as significant. The data from this experiment will be entered by Epidata3.1 and analyzed by SPSS 26.0 software.

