### Monitoring of adverse events

All adverse events that occur in our intervention will be monitored by researchers who are not involved in the data collection and have no conflicts of interest in terms of the data monitoring committee (DMC). Adverse events are defined as any untoward occurrences in study participants that are potentially related to the implementation of the study protocol. When a participant experiences an adverse event or a worsening of the disease, they will be immediately withdrawn from the trial, and statistical analysis will be performed with the existing data. The Ethics Committee will hold an annual meeting to monitor the execution of the entire trial.

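### An adverse event or worsening ends trial participation rather than treatment alone, so the 1-week outcome is lost for a reason that can depend on it

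*Protocol article*

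**What the plan says.** Monitoring of adverse events sets two triggers, an adverse event or a worsening of the disease, and one consequence: such patients "they will be immediately withdrawn from the trial, and statistical analysis will be performed with the existing data". Adverse events are defined as "any untoward occurrences in study participants that are potentially related to the implementation of the study protocol", with no severity threshold, so read literally a mild event also ends participation.

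The timing of outcomes is in Outcome measurements: "All assessments will be performed at the commencement of the study and after the 1-week intervention". The exceptions are sputum production and certain additional secondary outcomes. For sputum volume, Primary outcomes has the assessor "observe and record the volumes of sputum at the 1- and 24-h time points daily during the intervention period".

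Data collection, management, and analysis states "we will follow the principle of intention to treat (ITT) and use the sequence mean method to deal with the missing data". As a check on missing data it adds "we will compare participants who did not complete the intervention with those who completed the intervention". Sample size allows for loss: "we assume that the dropout rate of our trial will be about 20% after the week-long intervention".

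The description of the phonophoresis procedure is narrower. For skin burns or intolerance it halts the intervention and does not mention leaving the trial.

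**The concern.** Stopping a treatment protects the patient. Ending measurement adds no protection, and it removes the outcome that an intention-to-treat comparison needs. Here the loss is close to total for most endpoints. Viscosity (on which the trial is sized), vital capacity, FEV1%, SpO2, CAT and AIR have a single post-baseline measurement, at 1 week. Only the daily sputum volumes recorded before the event survive.

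The loss can also be informative. Worsening COPD triggers withdrawal, and most of these endpoints measure the state of the COPD, so whether a value is missing can depend on what it would have been. Nothing else in the protocol repairs this:

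- Mean fill gives a patient who worsened an average result.
- Comparing completers with non-completers can at most signal the problem, through baseline values and pre-event sputum volume.
- The dropout allowance protects numbers, not validity.

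This is a stated rule, not a detail left to an analysis plan. No analysis plan can recover an assessment that the protocol directs not to be made.

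**Working it through.** **Planning figure.** One-way ANOVA with 3 arms, effect size 0.4 (read as Cohen's f), alpha 0.15 and 90% power needs 20 per arm (power 0.905). Allowing for 20% dropout, 20 / 0.8 = 25 per arm, or 75 in total, which matches Sample size. The planned tests use 0.05. At that level 25 per arm gives 87% power and 20 per arm gives 78%.

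**Effect in SD units.** If the two comparators are equal and the combination is shifted by d, then f = d·√2/3, so d = 0.4 × 3/√2 = 0.849 SD.

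**Model for the rule (all rates are assumptions).** The outcome Y has SD 1, higher is better. A patient is withdrawn if Y plus independent noise of SD s falls below one threshold common to all arms, set to catch a share p of a comparison arm. The correlation between Y and the withdrawal score is ρ = 1/√(1+s²): 0.89, 0.71 and 0.45 for s = 0.5, 1 and 2. Available cases are analysed, so that the effect belongs to the withdrawal rule and not to the fill method.

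Among patients who stay, the comparison mean rises by ρ·φ(z)/(1−p), where Φ(z) = p. For the combination, z is replaced by z′ = z − d/√(1+s²).

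Worked case, p = 12%, s = 0.5:
- Comparison: z = −1.175 and φ(z) = 0.200, so the rise is 0.894 × 0.200/0.88 = 0.203.
- Combination: z′ = −1.175 − 0.849/1.118 = −1.934, so 2.7% are withdrawn and φ(z′) = 0.0615. The rise is 0.894 × 0.0615/0.973 = 0.057.
- Estimated effect: 0.849 + 0.057 − 0.203 = 0.70 SD.

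Simulation of 40,000 trials per setting (25 per arm, ANOVA at 0.05) agrees with this and supplies the power. Ranges run from strong to weak dependence of withdrawal on outcome:

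| Comparison arm withdrawn | Combination withdrawn | Estimate (true 0.85 SD) | Power | Power, same losses at random |
|---|---|---|---|---|
| none | none | 0.85 | 87% | – |
| 4% | 0.6-1.7% | 0.78-0.83 | 83-85% | 86% |
| 12% | 2.7-6.0% | 0.70-0.80 | 77-81% | 84-85% |
| 20% | 5.5-11.2% | 0.64-0.79 | 70-77% | 80-82% |

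Losses at random leave the estimate at 0.85 SD, so the last column separates lost numbers from lost validity. In an arm of 25, 12% is three patients.

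**No true effect, common rule.** All arms are truncated alike: bias 0.00, rejection 5%.

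**No true effect, outcome-linked withdrawal that differs by arm.** Take 12% / 0% / 12% for combination / breathing / phonophoresis. The spurious difference between combination and breathing is ρ × 0.200/0.88 = ρ × 0.227, that is 0.10-0.20 SD. Against the average of both comparators it is half that, 0.05-0.10 SD, and against phonophoresis it is 0.00. ANOVA rejects in 6-11% of trials.

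**Why mean fill is left out.** If the sequence mean is the overall observed mean, it shrinks the effect by itself: a purely random 12% loss in every arm gives 0.88 × 0.849 = 0.75 SD.

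**The case against.** The strongest case against concerns weight, not the reading of the text.

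- **Few events.** Eligibility excludes "Presence of acute exacerbation of COPD or on a rehabilitation program" and requires stable vital signs. Exposure is one week, and the Discussion expects little dropout in hospital. At 4% the loss is small, and nothing supports assigning the whole 20% allowance to worsening. This stands, and it is why the size is left open.
- **Conservative direction.** Under a common rule the error works against the combination, and with no true effect there is none. This also stands. An understated benefit is still a wrong estimate.
- **Weak mechanism for the differential case.** The only arm-specific events the protocol names are phonophoresis skin burns or intolerance. A burn may be unrelated to the outcome; such a loss costs patients but does not bias available cases. The 12% / 0% / 12% pattern is therefore only an illustration.
- **Baseline adjustment.** The plan also includes a model adjusted for baseline. With an assumed baseline-outcome correlation of 0.7, the 12% case gives 0.77-0.83 SD; with 0.5, 0.74-0.82 SD. Adjustment reduces the distortion without removing it.
- **Planned analysis.** The table describes available cases, not the planned mean fill. That is true and deliberate, to isolate the effect of the rule.
- **Unseen table.** The legend of Table 1 lists close-out and discharge time points, and the table body is not available. An exit assessment cannot be ruled out, but the text on timing and on withdrawal provides for none.

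**Conclusion.** The concern holds and should be fixed. Followed exactly, the rule discards the 1-week results of patients who worsen, against the protocol's own intention-to-treat principle, and nothing else in the plan recovers them.

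Size and direction cannot be known from the documents. If a common rule removes 4% to 20% of comparison patients and the true effect is the planning effect, an unadjusted available-case analysis loses between about 0.02 and 0.21 SD of a 0.85 SD benefit. These figures rest on assumed rates, normal outcomes and equal comparators. A false benefit needs outcome-linked withdrawal that differs between arms, for which the protocol gives no clear mechanism.

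**What to change.** Replace the withdrawal sentence in Monitoring of adverse events with:

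> An adverse event or worsening of disease may stop the study treatment but does not end participation. The 1-week (or discharge, if earlier) assessments are still made where clinically feasible and analysed in the randomised arm, unless the patient withdraws consent. If an assessment cannot be made, the reason is recorded.

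Leave the criteria for stopping treatment as they are.

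The cost is a short amendment and case report form wording for patients still to be enrolled. Extra assessments number at most about 0.20 × 75 = 15, if the whole dropout allowance came from this rule. They are assessments already scheduled, in inpatients.

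Recovery will be partial. Spirometry needs three to eight attempts, so some worsened patients will remain unmeasured, although SpO2, CAT and AIR need no forced manoeuvre. Rescue treatment before day 7 may also affect the values. If half of the lost assessments are made, the 12% case moves from 0.70-0.80 SD to 0.78-0.83 SD when recovery is random, but only to 0.76-0.82 SD when the more severe half stays unmeasured. Both ranges ignore rescue treatment.

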### Patient and public involvement (PPI)

Patients and the public will not be involved in the processes of recruiting, randomizing, allocating, conducting interventions, and collecting outcomes. However, COPD patients who are not participants in the study may be involved in the test to discover other unintended effects of phonophoresis before the start of the trial. In addition, to avoid adding to the research burden, the outcomes of the study were selected in line with the priorities and preferences of patients.

### Ethics and dissemination

There is no anticipated harm and will be no compensation for trial participation. Research reports will be disseminated through scientific forums, including peer-reviewed publications and presentations at national and international conferences. The datasets analyzed during the current study will be available from the corresponding author on reasonable request.

## Discussion

The study will explore the efficacy of a program combining the active cycle of breathing technique and phonophoresis in patients with COPD. The purpose of our study is to investigate whether the combined treatment can improve sputum viscosity, expectoration, and lung function.

Over-production and increased viscosity of sputum is common among COPD patients. Previous studies have attempted to solve these problems with active cycle of breathing techniques, without entirely satisfactory results [15–17]. It can be seen from previous reports that airway clearance is a complex process, and adequate expectoration may take a long time to resolve satisfactorily [47]. We thus propose an intervention program of active cycle of breathing techniques combined with phonophoresis to explore the best way for sputum management among COPD patients. Airway clearance techniques [48], medication [49], and rehabilitation exercise training [50] are effective in the removal of sputum. Researchers have, therefore, combined exercise training with physiotherapy applied to young patients with cystic fibrosis, a comprehensive intervention project that has resulted in significant improvements on sputum production, oxygen saturation, and short-term lung function [48]. The application of active cycle of breathing techniques combined with phonophoresis in COPD patients is not well documented. Phonophoresis can markedly enhance the effectiveness of drugs in the acute exacerbation of inflammation and pain and has received increasing attention recently [51–55]. We hope that the outcomes will be optimized by promoting more effective absorption of the drugs and the comprehensive program can play a complementary role in the treatment of COPD patients.

Due to the high incidence of COPD [8], it is likely that participants for this study will be relatively easy to recruit. In addition, the establishment of a pulmonary rehabilitation training center can provide practical guidance for the implementation of interventions. Previous research results are also able to provide us with a theoretical basis. Svenningsen et al. [45] reported a cross-over control trial of COPD airway clearance in which the loss on follow-up in the intervention and control groups was 12.50% and 18.75%, respectively, while Nicolini et al. [46] found that the loss on follow-up of the intervention groups 1 and 2 and the control group were 12.50%, 10%, and 17.50%, respectively. However, the dropout rate is unlikely to be high in our study, as it is conducted in the hospital where the rate of loss of study participants is certainly lower than that outside the hospital.

There are limitations to our research. Firstly, this is a single-center randomized clinical trial, and it is unclear whether our findings are generalizable to other locations and clinical settings. Secondly, as the study is of relatively short duration, no data will be available beyond 1 week and longer-term effectiveness will not be able to be evaluated.

In summary, this study introduces a combination of active cycle of breathing techniques and phonophoresis to explore the impact on patients hospitalized with COPD. If this comprehensive intervention is shown to be effective, it may prove to be a better treatment for patients with COPD.

### Trial status

When the manuscript is completed, the trial is in the recruitment stage. Our recruitment started in December 2019. This protocol is version 1.0, dated 25 December 2019. The end of the trial is expected in June 2021.

## Data Availability

The clinical data collected will not be shared with the public. However, non-clinical data will be shared with the public and other researchers.

## Abbreviations

COPD: Chronic obstructive pulmonary disease
CAT: Chronic obstructive pulmonary disease assessment test scale
AIR: Anxiety Inventory for Respiratory Disease Scale
AARC: American Association for Respiratory Care
GOLD: Global Initiative for Chronic Obstructive Lung Disease
ACBT: Active cycle of breathing technique
PPI: Patient and public involvement
FEV1%: Forced expiratory volume in 1 s to forced vital capacity
SpO_2_: Pulse oxygen saturation
